## Abstract

**Background:**

Hepatitis C virus (HCV) infection is a major cause of chronic liver disease and death. Drug use remains the significant cause of new infections in the European Union, with estimates of HCV antibody prevalence among people who inject drugs ranging from 5% to 90% in 29 European countries. In Ireland and the European Union, primary care is a key area to focus efforts to enhance HCV diagnosis and treatment among people who inject drugs.

**Objective:**

The Heplink study aims to improve HCV care outcomes among opiate substitution therapy (OST) patients in general practice by developing an integrated model of HCV care and evaluating its feasibility, acceptability, and likely efficacy.

**Methods:**

The integrated model of care comprises education of community practitioners, outreach of an HCV-trained nurse into general practitioner (GP) practices, and enhanced access of patients to community-based evaluation of their HCV disease (including a novel approach to diagnosis, that is, Echosens FibroScan Mini 430). A total of 24 OST-prescribing GP practices were recruited from the professional networks and databases of members of the research consortium. Patients were eligible if they are aged ≥18 years, on OST, and attend the practice for any reason during the recruitment period. Baseline data on HCV care processes and outcomes were extracted from the clinical records of participating patients.

**Results:**

This study is ongoing and has the potential to make an important impact on patient care and provide high-quality evidence to help GPs make important decisions on HCV testing and onward referral.

**Conclusions:**

A substantial proportion of HCV-positive patients on OST in general practice are not engaged with specialist hospital services but qualify for direct-acting antiviral drugs treatment. The Heplink model has the potential to reduce HCV-related morbidity and mortality.

**Registered Report Identifier:**

RR1-10.2196/9043

## Introduction

### Hepatitis C as a Global Challenge

With approximately 71 million people affected worldwide and 399,000 related deaths, chronic hepatitis C virus (HCV) infection is associated with considerable morbidity, including cirrhosis and hepatocellular carcinoma [1]. Injecting drug use remains the significant cause of new infections in the European Union, with estimates of HCV antibody prevalence among people who inject drugs (PWID) ranging from 5% to 90% in 29 European countries [2]. With successful treatment and viral eradication, recent data have demonstrated decreases in all-cause mortality, mortality due to cirrhosis, and the incidence of hepatocellular carcinoma [3-5].

Recently developed HCV direct-acting antiviral drugs are well tolerated and delivered for shorter courses (8-12 weeks), with trials reporting more than 90% cure rates among PWID [6]. Despite these highly effective and simplified therapeutic regimens, many people at risk are unaware of their infection, and obstacles limit access to HCV care, resulting in many patients not being treated [7].

Notwithstanding these challenges, the World Health Organization has set a goal of eliminating viral hepatitis as a major public health threat by 2030, reducing new chronic infections by 90% and reducing mortality by 65% [8]. In most countries, the scale-up of HCV treatment for PWID, along with needle and syringe programs and opiate substitution therapy (OST), will be key to these targets being achieved.

### Enhancing Access to Treatment

Reaching and engaging PWID with HCV are key challenges, given the prohibition surrounding illicit and injecting drug use and the resultant stigma and discrimination concerns and possible mistrust of health services [9]. Community and peer involvement is likely to be critical to the success of HCV prevention programs for PWID. It has also been hypothesized by some clinicians and researchers that successful treatment of HCV in PWID can improve recovery and engagement with addiction treatment [10].

Blood tests and liver biopsy were historically the standard approach to assess the need for treatment in those with chronic HCV infection. However, many patients have defaulted from HCV care because of perceived dangers associated with liver biopsy [11]. More recently, alternative diagnostic modalities including liver stiffness measurement by transient elastography (Echosens FibroScan Mini 430) have resulted in noninvasive approaches to stage fibrosis. Several European studies have recently reported on the feasibility of fibroscanning as a screening tool for drug users, with high rates of acceptance and uptake within various treatment and street outreach settings [12,13].The mobility of this equipment means it can be transported to community sites to access patients, and for PWID, this procedure can help assess disease severity, enhance HCV assessment, reduce patient identified barriers, target therapy, and enable the triage of patients for more immediate care [14-16].

### The Role of Primary and Community-Based Care

In Ireland and the European Union, primary care is increasingly providing long-term care for PWID. Although screening and identification practices are inconsistent, 62% to 81% of this population are infected with HCV [17,18]. Furthermore, research indicates 35% of patients attending general practitioners (GPs) for OST in Ireland also had problem alcohol use (PAU) [19], and a subsequent qualitative study highlighted the need for primary care to address this problem through screening and brief intervention [20]. The study recommended initial screening for PAU by the patient’s GP using the Alcohol Use Disorders Identification Test (AUDIT) screening tool [21] and providing feedback on results in all cases with positive findings through a brief intervention involving advice on minimizing alcohol harm, encouraging a reduction in alcohol consumption, and initiating referral to specialists when needed. Thus, primary care is a key area to focus efforts to enhance HCV diagnosis and treatment among PWID. However, a number of challenges exist in this regard, including for PWID: lack of awareness, fear of side effects for HCV drugs, possible poor adherence, and comorbid conditions; and for health care providers, limited knowledge and communication difficulties may be problematic [16,22,23]. These challenges can be addressed through education, audit and feedback, and liaison nurse support [24,25]. Research has demonstrated that if adequately supported, primary care and specifically general practice could adequately screen for HCV [26]. Research indicates that offering primary care practice staff training on the epidemiology, diagnosis, and management of HCV infection, so increasing testing of HCV was cost-effective [27]. Furthermore, testing PWID in primary care may also identify patients who have been diagnosed previously but have not been referred to, or failed to attend specialist care, offering the opportunity to review and follow-up such referrals.

### Aims

This Heplink study forms part of a European Union–funded program of research (HepCare Europe) which aims to optimize hepatitis C diagnosis; linkage between primary, secondary, and outreach community care; and access to treatment for at risk-populations in the European Union.

The Heplink study focuses specifically on developing complex interventions to enhance community-based HCV treatment and improve the HCV care pathway between primary care and secondary care. As such, Heplink is a prospective, nonrandomized pre-post intervention feasibility study in primary care to identify and invite patients on OST to undergo testing, with referral to secondary care, where appropriate. We will evaluate the feasibility, acceptability, and likely efficacy of this approach quantitatively, qualitatively, and through assessing its cost-effectiveness. The specific objectives of the study are to develop and implement an integrated model of HCV care and evaluate its feasibility, acceptability, likely efficacy, and cost-effectiveness in practice.

## Methods

### Study Design and Setting

This is a prospective, nonrandomized, pre-post intervention feasibility study to be conducted in OST-prescribing general practices from three sites across the Hepcare Europe consortium (Dublin, London, and Seville). Practices will be given written information on the study and asked to indicate their interest in participating. Our recent experience recruiting general practices [28,29] has taught us the importance of a researcher promptly following up an expression of interest from a GP to fully explain the study and highlight what will be required from the GP in terms of time and commitment to the study. As such, practices who express an interest in participating will be contacted by a member of the research team to explain the aims of the study and what is required.

### Study Population

A sample of 24 OST-prescribing GP practices will be recruited from the professional networks of members of the research consortium.

Practices will be eligible to participate if they are registered to prescribe methadone and have at least 10 patients currently receiving OST; agree to participate in practice audit; and (3) agree to facilitate nurse liaison.

Patients (n=240) will be eligible to participate if they are on OST (ie, methadone); are aged at least 18 years; and attend the practice for any reason during the recruitment period.

### Approach to Sampling and Recruitment

A standardized nonprobability sampling framework will be used to identify 10 consecutive patients from each practice or center to participate in the study. On the basis of the recommendations for good practice in feasibility studies [30] and our previous work conducting feasibility studies with PWID [29,31], we estimate that 240 patients (attending 24 general practices) will be adequate to calculate the actual recruitment and retention rates (ie, feasibility) and provide data on acceptability of study processes and outcome measures, which will inform a future definitive trial. This approach to recruitment reflects the challenges involved in recruiting this population group for projects. Patients who consult a doctor or nurse in participating practices or centers and who are eligible for the study will be given written information and a verbal explanation of the study, including the study purpose, procedures, and how findings will be utilized. Those who are interested in participating will be asked to sign a consent form, which will be witnessed by the doctor or nurse or the researcher. Although the initial approach to participate will be from a health care professional, recruitment will be facilitated by a member of the research team being “on site” to support the practice during the recruitment phase and answer any questions potential participants may have. The recruitment phase will involve each participating practice engaging in an intensive, 4-week period of patient recruitment, an approach we found most effective in previous work with this population [28,29]. During this 4-week period, the member of the research team will aim to (1) obtain contact details for and informed consent from eligible patients, (2) review the clinical records of patients who consent to participate in the study, and (3) collect baseline data, including patient demographics and current care process and outcome measures from clinical records.

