### Data Collection

Data on patient demographics and HCV care processes/outcomes will be extracted from the patient’s clinical electronic or paper medical record and also from patient self-reported data collected through the HCV liaison nurse assessment to include the following:

Prior HCV testingHCV status—antibody and Ribonucleic Acid (RNA) or antigenReferral and attendance for HCV care at a hospital’s Department of Hepatology or Infectious DiseasesHCV assessment and treatment and sustained virological response (SVR)Alcohol screening and brief intervention using a validated alcohol screening instrument (eg, AUDIT)Other blood borne virus (BBV): HIV and hepatitis B virus (HBV)BBV testing/vaccination: liaison nurse will assess if the patient has been tested for HCV, HIV, and whether HBV immunization is requiredChronic illnessMortality

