**Figure 1 figure1:**
[figure not shown]
Flowchart of the nurse-led intervention. GP: general practitioner; HCV Ab: HCV antibody; HCV: hepatitis C virus; ID: infectious diseases; MMUH: Mater Misericordiae University Hospital; PCR: polymerase chain reaction; OPD: Outpatient Department; OST: opiate substitution therapy; RNA: Ribonucleic Acid; Ag/RNA: Antigen/Ribonucleic Acid.

The HCV liaison nurse will meet and assess the patient, addressing any questions they may have regarding their HCV status. The liaison nurse will also gather data on the following variables:

HCV risk factors (eg, incarcerated, tattoos, piercings, blood transfusion, sexually transmitted infection test)OST treatmentAlcohol use assessed using the AUDIT questionnaireHCV testing, assessment, and treatment historyOther BBV testing and HBV and hepatitis A virus vaccination historyQuality of life (EQ5D-3L)—collected by HCV liaison nurse just before their assessment and intervention where necessary with each patientHCV-antibody positive and Ribonucleic Acid/Antigen (RNA/Ag) status (positive or unknown)Echosens FibroScan Mini 430 data (the nurse will have received Echosens FibroScan Mini 430 training)

After the assessment, the liaison nurse will provide the patient with information/education regarding HCV, including how it is transmitted and how to prevent transmission. Harm reduction strategies will also be addressed if required. A handover of the nurse’s assessment will be given to the GP. HCV Ab+ patients will be referred to specialist services if they are Ag+, RNA+, or if Ag and RNA status are unknown. This process will be carried out by the GP with the assistance of the HCV liaison nurse. Referrals are submitted to the hospital’s Hepatology or Infectious Diseases department.

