Feasibility	Compare pre-post intervention data on patient demographics, hepatitis C virus (HCV) care processes and outcomes extracted from patients’ clinical electronic or paper medical records, and also from patient self-reported data collected through the HCV liaison nurse assessment; patient recruitment rates; patient retention level; and cost-effectiveness of the intervention	Compare pre-post intervention data on patient demographics, HCV care processes and outcomes extracted from patients’ clinical electronic or paper medical records, and also from patient self-reported data collected through the HCV liaison nurse assessment; practice recruitment rates; practice retention level; cost-effectiveness of the intervention
Acceptability	Patients’ experience of intervention evaluated by analysis of semistructured interviews with patients	GPs’^a^ and practice nurses’ experience of intervention evaluated by analysis of semistructured interviews with patients
Likely efficacy	Although not adequately powered to examine efficacy, possible efficacy will be assessed by proportion of patients who have been screened for HCV and alcohol use, proportion of patients who have been referred for treatment (HCV, alcohol), and cost-effectiveness of study	Although not adequately powered to examine efficacy, possible efficacy will be assessed by knowledge and attitudes and practice pre-post intervention and cost-effectiveness of study

^a^GP: general practitioner.

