### Ethical Considerations

The study has been approved by the Mater Misericordiae University Hospital Research Ethics Committee (Ref: 1/378/1722) and the Research Ethics Committees of the collaborating institutions in London and Seville.

Ethical considerations and safeguards include the following:

Informed consent and consenting capacity: all potential participants (GPs, patients) will be given written information on the study, the model of care being proposed, and asked to provide written consent that they are happy to participate and that nonparticipation will not compromise their usual care. Participation in the study will be on a voluntary basis. No inducements to participate will be offered.Confidentiality: Any data/personal details that could potentially reveal the identity of individuals will be removed. Only anonymized, deidentified information will leave the practice of origin. To allow follow-up, an alphanumeric code will be assigned to each participant’s data; a database will be maintained on a password-protected database at Mater Misericordiae University Hospital. The list will be kept separately from patient data but will indicate the medical record number of each participant and the alphanumeric code. All research data will be stored on a password-protected desktop computer at the host organization. Study participants will be invited to give permission to have their name, address, and contact details held by the research team to facilitate their receiving a synopsis of the study findings on publication and to be contacted for follow-up data collection. All data will be stored securely at the host institution.Clinical governance, do no harm: it is possible that participating in the study may raise health-related issues for participants and may identify a health issue that requires a clinical intervention. Therefore, all participants will be advised to speak with their doctor if participating in the study has raised any such issues. At the conclusion of the intervention, the HCV-trained liaison nurse will conduct a handover of clinical information to the GP, which includes recommendations for follow-up care.

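### Stated data sources disagree (baseline from records; pre-post comparison also from nurse-elicited self-report), so old unrecorded care can appear as change

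*Protocol article*

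**What the plan says.** **Baseline.** Under Approach to Sampling and Recruitment, a researcher will, in the 4-week recruitment phase, "collect baseline data, including patient demographics and current care process and outcome measures from clinical records". The Methods part of the abstract agrees: "Baseline data on HCV care processes and outcomes were extracted from the clinical records of participating patients".

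**The data set and the pre-post comparison.** Data Collection names the medical record as one source of care-process and outcome data "and also from patient self-reported data collected through the HCV liaison nurse assessment to include the following". The list that follows covers prior HCV testing, HCV status, referral and attendance, treatment and sustained virological response. Table 1, in its feasibility row, names the records for the pre-post comparison "and also from patient self-reported data collected through the HCV liaison nurse assessment; patient recruitment rates".

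**The nurse visit.** Outreach by the liaison nurse is the first component listed under Intervention. The text below Figure 1 has the nurse take the patient's history of HCV testing, assessment, treatment and vaccination. Then: "A handover of the nurse’s assessment will be given to the GP". Ethical Considerations adds that, when the intervention ends, "the HCV-trained liaison nurse will conduct a handover of clinical information to the GP".

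**The outcomes and the test.** Outcome Measures words the primary outcomes cumulatively, with no date window: the share of participants ever screened, and the share of antibody-positive patients who started or completed therapy or reached a sustained response. Data Analysis compares pre and post with the Fisher exact test. Study Design and Setting describes a nonrandomized pre-post study, so there is no control group.

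**The concern.** In a pre-post study the two measurements must have the same chance of finding an event that has already happened. Here the baseline passages describe a records search, while the comparison passages add a second source that exists only because the intervention sends a nurse to ask. Suppose a patient was tested years ago at a hospital or prison, and the practice notes do not show it. A records search gives no; the nurse's history gives yes. If the first answer serves as pre and the second as post, the comparison registers a gain although no care was delivered.

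Without a control group, nothing in the design nets this out. The estimates also have further uses. Outcome data from the intervention feed the cost-effectiveness model, whose result is judged against €45,000 per QALY for Ireland, and the Conclusions expect the study to supply parameters for a cluster randomized trial. A shift due to ascertainment would carry into both.

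**Working it through.** **1. Sample size.** 24 practices × 10 patients = 240, which reproduces the planned number. It is a feasibility size with no power calculation, so there is no effect size or power figure to check.

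**2. Sources by time point, as stated.**

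| Place | Time point | Source |
|---|---|---|
| Abstract, Methods | baseline | records |
| Approach to Sampling and Recruitment | baseline | records |
| Data Collection | not assigned | records and nurse self-report |
| Table 1, feasibility | pre-post comparison, not split | records and nurse self-report |
| Any section | follow-up alone | not stated |

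If the last two named sources serve both time points, they disagree with the first two rows. If self-report enters only after baseline, ascertainment differs between periods. Either way the passages need reconciling.

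**3. Size for the screening outcome, with no new tests.** The article gives no figure for record completeness, so the starting rates (70%, 80%) and the share of patients with a recovered old test (5%, 10%, 15%) are assumptions. The test is the plan's own, two-sided Fisher exact, 240 patients pre and 240 post.

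| Recovered | Pre → post | Counts | p |
|---|---|---|---|
| 5% (12 patients) | 70% → 75% | 168 → 180 | 0.26 |
| 5% | 80% → 85% | 192 → 204 | 0.19 |
| 10% (24 patients) | 70% → 80% | 168 → 192 | 0.015 |
| 10% | 80% → 90% | 192 → 216 | 0.003 |
| 15% (36 patients) | 70% → 85% | 168 → 204 | 0.0001 |

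**4. The same artefact as a formula.** Let p be the true share screened before the study, s the share of that care visible in the records at baseline, and r the share of the missed care recovered later. Then pre = p·s, post = p·(s + (1 − s)·r), and the spurious gain is p·(1 − s)·r.

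- p = 0.75, s = 0.90, r = 0.5: 67.5% → 71.25%, a gain of 3.75 points (Fisher p = 0.43).
- p = 0.75, s = 0.80, r = 0.5: 60.0% → 67.5%, a gain of 7.5 points (p = 0.11).
- p = 0.75, s = 0.80, r = 1: 60.0% → 75.0%, a gain of 15 points (p = 0.0006).
- Over p 0.60–0.90, s 0.70–0.95 and r 0.5–1, the gain runs from 0.60 × 0.05 × 0.5 = 1.5 points to 0.90 × 0.30 × 1 = 27 points.
- With complete records (s = 1) or no recovery (r = 0), it is zero.

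**5. Outcomes among HCV-positive patients.** Here the nurse's history can add to the denominator as well as the numerator. Take 45 treated of 150 known positives (30%) as an assumed baseline, and let 24 previously unrecorded positives be recognised.

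- If 5 of the 24 had been treated: (45 + 5)/(150 + 24) = 50/174 = 28.7%, a fall.
- If 12 of the 24 had been treated: (45 + 12)/174 = 57/174 = 32.8%, a rise.

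For newly recognised positives, the sign depends on whether their treated share lies above or below the baseline 30%. Recovered treatment in patients already known to be positive pushes the other way from the first example: numerator up, denominator unchanged. The net direction is not fixed.

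**The case against.** The strongest reply is that the article never says follow-up status rests on self-report. Data Collection and Table 1 name two sources without tying either to a time point. A history taken by the nurse is by nature information about the past, so it could well be intended as baseline data, in which case nothing moves from no to yes. The recruitment passage describes a researcher's task and does not say that records are the sole baseline source. This stands as far as it goes: a reader might infer that old care **will** be counted as improvement, and the text does not support that. It supports only that it **can** be.

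Three further inferences are tempting and also fail:

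- **That handed-over history enters the record that is later extracted.** The text says it goes to the GP, not that it is written into the notes.
- **That both primary outcomes are biased towards benefit.** This is arguable for screening. It is not established for treatment and sustained response, as step 5 of the working shows.
- **That the artefact cannot be separated from real change.** It can be, if events are dated.

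It may also be said that extraction rules belong in a full protocol or SAP that is not shown, and that the study states it is not powered for efficacy. The first does not dispose of the point, because the article itself states sources that disagree. The second rightly lowers the weight to be given to p-values, but bias does not depend on power, and the article still plans pre-post estimates of likely efficacy.

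**Conclusion.** The point holds as a conflict between stated data sources that leaves ascertainment unprotected between the two periods. Unrecorded past care can register as change: upward for HCV screening, blood-borne virus testing and immunization; in either direction for outcomes with HCV-positive patients as denominator.

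The size is illustrative only. At an assumed 5% recovery the screening artefact would not reach conventional significance under the plan's test; at 10% it would. The article gives nothing to decide between them. Outcomes such as key-informant experience and staff knowledge are not affected by this mechanism. Given the feasibility purpose and the small effort needed, this is a cheap improvement, and it is worth making on either reading of the source passages.

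**What to change.** 1. Reconcile the abstract and Approach to Sampling and Recruitment with Data Collection and Table 1, naming the source that serves each time point.
2. Base the main pre-post comparison on one source at both times: documented, dated results.
3. Classify every event, including HCV-positive status, by the date it occurred and not the date it was learned. Events before a stated index date, including those the nurse elicits, count as baseline. This rule is needed even with a records-only comparison, because handed-over history might be written into the notes between the two extractions.
4. Report a sensitivity analysis with self-reported history added to both periods.

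The cost is an analysis rule plus event-date and source fields on the extraction form. The downside is that some undated self-reports leave the main comparison, and the apparent improvement may be smaller. Data collection was due to end in July 2018; where dates are already in the records, the rule could be applied at analysis.
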